### Data analysis

The analysis will be implemented in SAS Institute Inc (2023). For all analyses at baseline and final follow-up time, descriptive statistics (e.g., frequency, central trend, and variability) and diagnostic plots (e.g., histogram or kernel density estimation and q–q plots) will be implemented on all variables. Data for outliers will be evaluated and tested as needed for statistical model assumptions. Appropriate corrective strategies, such as transformations, the use of robust methods, and/or data reduction, will be used if problems are identified.

These preliminary analyses aim to ensure high-quality data and test the assumptions of the proposed statistical models. We assume that this study (cohort) suffers from an uneven distribution of confounding factors, which may be exacerbated by the bias due to the possible unequal dropout rates between exposure groups. Therefore, adequate adjustment of the characteristics of the study subject is crucial to make an unbiased inference of the associations between the outcomes of interest (addiction, falls, and mortality) and the main exposure factor, IC, and the associations between IC and its five domains (vitality, mobility, sensory, cognitive, and psychological) and the evolution of IC in the follow-up time.

It is also expected that not all values for all variables will be collected, thus generating observations with missing values. If there is a substantial number of unused cases under analysis due to missing values (≥5%), multiple imputations of these values will be used along with a corresponding sensitivity analysis. In the sensitivity analysis, models with the inclusion of imputed missing data will be compared to original models in which missing data are not included. If there is a substantial change in the parameters of interest between these two models (e.g., a nonsignificant coefficient in the original model becomes significant in the model with imputed data), the imputed model will be accepted as the least-biased model in terms of the bias introduced by the missing values of variables.

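### The missing-data rule lets a change in significance decide which model is accepted and does not say which model is reported otherwise

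*Protocol article*

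**What the plan says.** The rule is in the protocol article, section Data analysis. Its trigger is that at least 5% of cases would be unused because of missing values. In that event "multiple imputations of these values will be used along with a corresponding sensitivity analysis". The sensitivity analysis is a comparison: "models with the inclusion of imputed missing data will be compared to original models in which missing data are not included". The decision follows: "If there is a substantial change in the parameters of interest between these two models", for which the one illustration is that "a nonsignificant coefficient in the original model becomes significant in the model with imputed data", then "the imputed model will be accepted as the least-biased model in terms of the bias introduced by the missing values of variables".

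The section gives no threshold for a substantial change. It does not mention a coefficient that loses significance. It does not say which model is reported when the two do not differ substantially, and it calls neither model primary.

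The paragraph before it names "the bias due to the possible unequal dropout rates between exposure groups" as something that may make confounding worse.

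**The concern.** The model that is accepted depends on results already seen, and the criterion illustrated is a p-value crossing 0.05. That is not evidence about bias. Imputation restores sample size, so a coefficient can become significant with no change in its value. Conversely, a large shift between two significant estimates, which would be a real warning of bias, is not the case that the example describes.

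The rule also leaves a gap. With no substantial change, the reader cannot tell which estimate will be published.

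Two things are at stake: control of the type I error in each test, and a clear primary estimate. The exposures planned are TIC, DIC and WIC, and the outcomes are ADL/IADL loss, falls and death, so the choice recurs over many tests. It may also reach the WIC score itself, because significance decides there whether a coefficient receives a scaled weight or a single point.

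**Working it through.** **Inputs.** From the article: the 5% trigger (Data analysis); α = 0.05 and a planned dropout of about 15% (Study sample size and power calculation); 500 of 1,600 members lost in 2 years in an earlier cohort (Discussion), which is 500/1,600 = 31%. Assumed, because the article gives no figure: the fraction m of cases missing from the complete-case model, taken from 5% to 50%.

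**The plan's own figure.** The missing-data rule states no error rate. The sample-size section does not say whether α is one- or two-sided, so I checked Table 1 (RR 1.91, incidence 0.0495, stated 514 per group). With p₀ = 0.0495, p₁ = 1.91 × 0.0495 = 0.0945 and unpooled variance:

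n = (1.960 + 0.842)² × [p₀(1−p₀) + p₁(1−p₁)] / (p₁−p₀)² = 7.849 × 0.1327 / 0.002029, which rounds up to 514.

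This matches; a one-sided test (pooled variance) would give 407. I therefore use two-sided 5%, with critical value 1.96.

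**Significance can change while the estimate does not.** If imputation recovered all the lost information and left the coefficient unchanged, z would grow by 1/√(1−m). At m = 0.15, any complete-case |z| between 1.96 × √0.85 = 1.81 and 1.96 would become significant.

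**Two readings of the rule.** Reading A switches to the imputed model only when significance is gained, as in the example, and otherwise keeps the complete-case model. Reading B accepts the imputed model after a change of significance in either direction.

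| Complete-case | Imputed | Final result, A | Final result, B |
|---|---|---|---|
| significant | significant | positive | positive |
| not | not | negative | negative |
| not | significant | positive | positive |
| significant | not | positive | negative |

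Under B the final result is always that of the imputed model. Under A it is positive if either model is significant. The readings differ only in the last row.

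**Type I error under A.** Take two null statistics, bivariate normal with correlation ρ = √(1−m). The error is 1 − P(|Z₁| ≤ 1.96 and |Z₂| ≤ 1.96).

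| m | ρ | Error, A |
|---|---|---|
| 5% | 0.975 | 0.060 |
| 10% | 0.949 | 0.065 |
| 15% | 0.922 | 0.068 |
| 30% | 0.837 | 0.076 |
| 50% | 0.707 | 0.083 |

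**Simulation.** The set-up was a null exposure, a confounder with missing values, 10 imputations pooled by Rubin's rules, n = 1,000 and 3,000 runs per setting (Monte Carlo standard error 0.004 to 0.005). In the missing-at-random runs, missingness depended on the outcome.

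| m | A, missing completely at random | A, missing at random |
|---|---|---|
| 5% | 0.060 | 0.071 |
| 15% | 0.069 | 0.069 |
| 30% | 0.075 | 0.072 |
| 50% | 0.077 | 0.080 |

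Under B, or with the imputed model fixed in advance, the simulated error was 0.046 to 0.057, compatible with the nominal 0.05.

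**The case against.** The strongest defence is that the operative criterion is a substantial change in the parameters, and gained significance is only an example. A reader might infer that the rule necessarily inflates false positives. The text does not support that: under Reading B there is no inflation.

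A reader might also infer that the complete-case model is the default. The label given to that model and the conditional acceptance of the other point that way. But the section also says that imputation will be used at 5% or more, which can be read as making imputation the planned analysis. The default is not stated. Nor does the rule ever select the complete-case model because it is the significant one; the only stated switch is towards imputation.

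It is also tempting to say that nearly every follow-up model will meet the trigger, given the 31% lost in the earlier cohort. That goes too far. The main outcome models are Cox models, in which a participant who drops out without an event contributes time up to the last evaluation and is not thereby an unused case. The article also lists measures to reduce loss. For ∆IC and DIC, which need a follow-up measurement, the planned 15% dropout would by itself exceed 5%.

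Finally, the article calls unequal dropout possible, not expected. Dropout that differs by exposure does not alone bias a regression that conditions on exposure, so that sentence does not prove the complete-case estimates biased.

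These points limit the claim but do not rescue the rule. It is a decision rule written into the article, not a detail left to an analysis plan. On either reading it uses a criterion that does not measure bias and leaves the reported model open.

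**Conclusion.** The point holds in a limited form. The rule lets results decide which model is accepted, illustrates the decision only by a gain in significance, leaves a substantial change undefined, and is silent on what is reported otherwise.

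Inflation is conditional. It needs a one-directional switch and the complete-case model kept in all other cases. Then the type I error per test is about 6–8% instead of 5%, an excess of roughly 1 to 3 percentage points, and 1.8 points at 15% missing. These figures rest on an assumed missing fraction of 5–50% and on ρ = √(1−m). If imputation recovers less information than that formula supposes, the two statistics are more highly correlated and the excess is smaller. If a change in either direction selects the imputed model, there is no excess, and the criterion serves no purpose for the significance decision.

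**What to change.** State in advance that, when at least 5% of cases would be unused because of missing values, the multiply imputed model is the primary analysis. Report the complete-case model beside it as a sensitivity analysis, whatever either p-value shows. Delete the sentence that accepts a model because of a change in significance.

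The cost is one paragraph of wording. Both models are already planned, so no analysis is added, and the Data Availability statement says that no data have been collected, so the change can still be made before any result is known.

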### Generation of weighted IC score (WIC)

To build the weighted IC score (WIC), first, associations between subdomains of IC domains (sensory, mobility, vitality, cognitive, and psychological) and IADL loss will be evaluated by IADL models in a two-stage logistic regression (Meng et al., 2022). For this purpose, IC subdomains will be dichotomized, such as body mass index (BMI) (overweight–obese v. normal–underweight) and handgrip strength (normal–strong v. weak), both of which are subdomains of the vitality domain (Chen et al., 2020). The first stage of modeling requires bivariate analysis between each IC subdomain and IADLs to identify candidate subdomains to enter the multivariate logistic model (Meng et al., 2022). For this, the variable in the model whose *p-*value for the statistical test of association (chi-square) with IADL is less than or equal to α = 0.25 will enter the multivariate logistic regression model with adjustment for the sociodemographic, comorbidity, behavioral, and clinical factors. An exception will be variables selected *a priori* since they are clinically fundamental, such as BMI from the vitality domain.

In the multivariate logistic regression model, subdomains whose *p-*values are less than or equal to α = 0.05 (statistically significant) will be used to generate WIC as follows. For the regression coefficient in the multivariate model that reaches statistical significance (*p ≤* 0.05), its component will be transformed into a subdomain score by dividing the coefficient by the smallest regression coefficient in the model after rounding the absolute value of the coefficient to the nearest integer value. Regression coefficients that are not statistically significant in the adjusted model will have a value of one (1) point. A summary WIC will be obtained by adding points from all regression components. The subdomain terms will enter the multivariate regression model such that the higher the WIC score, the better the IC.

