### Explanatory variables: IC composite index (ICI)

An IC composite score or index (IC index or ICI) will first be created, as suggested by Gutiérrez-Robledo et al. (2019). This score aims to express a summary measure of impairments for an older adult. Initially, each continuous or ordinal subdomain measure will be dichotomized based on acceptable cut-off points to create a binary variable of 0 or 1 (see Table 3 for cutoff points across all subdomain measures). Within a domain, the values of these recoded subdomain measures will be summed up to create a “subdomain score.” The subdomain scores will range from 0 to 2 for the four subdomains with only two measures and from 0 to 6 for the subdomain with six measures (i.e., vitality). Then, each domain of the five IC components will be subdivided into three categories based on the sum of the scores of its subdomains, with the following numerical score: no impairment = 0, mild impairment = 1, and severe impairment = 2. For example, the four domains with only two subdomain measures (e.g., cognitive with subdomain measures memory and cognitive) will be coded 0 if their subdomain score (sum of their subdomain measure) is 0, 1 if the subdomain score value is 1, and 2 if the subdomain score value is 2. The domain with six subdomain measures, vitality (subdomains comorbidity, medication, biomarkers, pain, strength, and nutrition), will be coded 0 if its subdomain score is 0, 1 if the subdomain score is 2–4, and 2 if the subdomain score is 5–6. Scores for each of the five domains will be summed up to produce a composite IC index ranging from 0 (best possible ICI) to 14 (worst possible ICI).

Subsequently, this baseline ICI will be classified in four ways. First, using the terciles of ICI (TIC), ICI values less than or equal to the first tercile (Q1) will be classified as low TIC; ICI values between Q1 and the third tercile (Q3), including Q3, will be classified as medium TIC; and ICI values above Q3 will be classified as high TIC. This analysis model is explicitly shown in Figure 1.

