Second, the change in the ICI value during the follow-up time in the cohort will be measured and referred to as “ICI delta” (∆IC). The ∆IC is calculated as the difference between the ICI measured in the last follow-up wave minus the ICI measure at the baseline (variable with values between 0 and 10). Third, we will consider the presence of a decline in IC (DIC) if one or more declines in an IC domain are found from the baseline measure. As an example of IC domain decline in the cognitive dimension, a Montreal Cognitive Assessment (MoCA) score of 22 at follow-up versus 27.0 at baseline is considered a decline and probable “dementia” (Nasreddine et al., 2005). The opposite will be classified as no decline.

Finally, a weighted measure of IC (WIC) will be derived from the multivariate regression result of the association between IC subdomains and IADL loss, which will be adjusted for individual sociodemographic factors (see the Analysis section below for detailed description of WIC).

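### The single BMI cut at 25 scores underweight as unimpaired, so the only nutrition item cannot register undernutrition and the WIC coefficient for BMI uses a mixed reference group

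*Protocol article*

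**What the plan says.** Table 3 dichotomises all subdomain measures. For BMI it gives one threshold: 25 or below scores 0, above 25 scores 1. There is no lower threshold.

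The section on the IC composite index (ICI) sets the direction of scoring at domain level: "no impairment = 0, mild impairment = 1, and severe impairment = 2". It lists the vitality items as "subdomains comorbidity, medication, biomarkers, pain, strength, and nutrition"; BMI is the only Table 3 entry that can stand for nutrition. The six items are summed and the domain is coded 0 for a sum of 0, then "1 if the subdomain score is 2–4, and 2 if the subdomain score is 5–6". A sum of 1 has no code. For change over time, "The ∆IC is calculated as the difference between the ICI measured in the last follow-up wave minus the ICI measure at the baseline".

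The section on the weighted IC score (WIC) describes the BMI contrast as "body mass index (BMI) (overweight–obese v. normal–underweight". BMI is exempt from the bivariate screen at p ≤ 0.25 because some variables are kept "since they are clinically fundamental, such as BMI from the vitality domain". In the adjusted model a significant coefficient is converted to points, and a non-significant one receives one point.

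**The concern.** The plan names underweight as a state but has no way of scoring it as an impairment. The rule is written out twice, in Table 3 and in the WIC section, and no other item (a lower BMI class or a weight-loss question, for example) makes up for it.

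Two uses of the item are affected. In the ICI and the measures built from it (terciles, change score, domain decline), undernutrition in people aged 60 and over is either invisible or, for those who start above 25, recorded as the loss of an impairment. In the WIC model the reference group pools two BMI classes that may differ in risk, so the weight given to BMI does not measure overweight against normal weight, and no underweight effect is estimated. Because BMI is forced into the model and earns a point even when non-significant, the selection procedure cannot remove a poorly specified BMI term.

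**Working it through.** The document gives no sample size, power or estimate that depends on the BMI cut, so there is no stated figure to reproduce. The check has three steps.

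**1. The item under Table 3.** Example BMI values at baseline and follow-up:

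| BMI change | Item | Scored as |
|---|---|---|
| 27 to 17.5 | 1 to 0 | improvement |
| 22 to 17.5 | 0 to 0 | no change |
| 27 to 24 | 1 to 0 | improvement |
| 22 to 27 | 0 to 1 | impairment |

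The first and third rows cannot be told apart. Improvement here means a fall on the ICI scale, where 0 is defined as best. Research question 1 labels a negative ∆IC a decrease in IC; that inconsistency of sign is a separate matter.

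**2. From the item to the ICI.** Let k be the sum of the other five vitality items, held fixed. When the BMI item falls from 1 to 0, the vitality sum goes from k + 1 to k.

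| k | Sum | Vitality code |
|---|---|---|
| 0 | 1 to 0 | uncoded to 0 |
| 1 | 2 to 1 | 1 to uncoded |
| 2 | 3 to 2 | 1 to 1 |
| 3 | 4 to 3 | 1 to 1 |
| 4 | 5 to 4 | 2 to 1 |
| 5 | 6 to 5 | 2 to 2 |

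Under the codes as stated, the ICI improves by one point only at k = 4. At k = 2, 3 and 5 it does not move. At k = 0 and 1 the result is undefined, because a sum of 1 has no code.

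**3. The WIC contrast.** Let s be the underweight share of the group at or below 25, RR_u the risk ratio of underweight against normal weight, and RR_o that of overweight–obese against normal weight. The risk in the pooled reference group is p0 × [1 + s(RR_u − 1)], so

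RR against the pooled group = RR_o / [1 + s(RR_u − 1)].

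Inputs: p0 = 0.0495 (Table 1, functional-loss incidence, average column), used here as the normal-weight risk; N = 5,500 × 0.85 = 4,675 (sample size section, 15% dropout). N does not enter the ratio. The document has no BMI distribution and no risk by BMI class, so the rest is assumed: 5% underweight, 45% normal, 50% overweight–obese, giving s = 0.05/0.50 = 0.10.

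| RR_u | RR_o | Pooled reference risk | RR against normal | RR against pooled group |
|---|---|---|---|---|
| 1.0 | 1.2 | 0.0495 | 1.20 | 1.20 |
| 2.0 | 1.2 | 0.0495 × 1.1 = 0.05445 | 1.20 | 0.0594/0.05445 = 1.09 |
| 3.0 | 1.2 | 0.0495 × 1.2 = 0.0594 | 1.20 | 0.0594/0.0594 = 1.00 |
| 2.0 | 1.0 | 0.05445 | 1.00 | 0.0495/0.05445 = 0.91 |
| 2.0 | 0.8 | 0.05445 | 0.80 | 0.0396/0.05445 = 0.73 |

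Whenever RR_u exceeds 1 the ratio is lowered. That is towards the null if overweight raises risk, away from it if overweight is protective, and a spurious association if overweight is neutral.

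**The case against.** The scoring rule itself has no defence in the document, but four objections to making more of it are sound.

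- A reader might infer that the BMI term in the WIC model is diluted towards the null. That needs excess risk of IADL loss in both BMI tails, and the document gives neither. The last two rows of the final table show movement away from the null.
- A reader might infer that ∆IC runs the wrong way for people who lose weight. In general it does not. The item falls only for those who start above 25, and under the stated codes the ICI follows only when the other five items sum to 4. Elsewhere the usual effect is that impairment is missed.
- A power comparison is tempting. Under the base assumptions (RR_u 2, RR_o 1.2) a test of the single cut has about 11% power and a three-level test about 82%. But the first is a one-degree-of-freedom test of overweight–obese against the rest, and the second a two-degree-of-freedom test of any difference. With RR_o = 1.0 the three-level power is still about 85%, so it comes mainly from the assumed underweight effect. With RR_u = 1.0 the single cut does better (32% against 25%). These figures do not measure power lost for the overweight coefficient.
- BMI is one of 14 binary items and one of six in vitality, institutionalised and bedridden people are excluded, and the share of underweight participants is not given. The effect on the index as a whole cannot be sized.

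These points limit the consequences. They do not answer the fact that the only nutrition item cannot register undernutrition.

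**Conclusion.** The point holds as a defect in a written scoring rule. That underweight scores as unimpaired, that a fall from above 25 into underweight lowers the item, and that a fall from normal weight into underweight leaves it unchanged all follow from the text without outside data. The carry-over to the ICI is confined to vitality boundary crossings: one point when the other five items sum to 4, and undefined where a sum of 1 arises.

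For the WIC, the document supports only that the BMI coefficient is a contrast with a mixed reference group, whose size and sign depend on an unestimated underweight share and risk. The move from 1.20 to 1.09 illustrates assumed inputs and is not an estimate for this cohort. If underweight carries no excess risk, pooling leaves the coefficient unbiased and only the scoring defect remains.

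**What to change.** In Table 3, use the three classes that the plan already names and score underweight as well as overweight–obese as 1. The authors should choose and justify the lower cut; none is proposed here.

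In the WIC model, replace the single BMI term with two binary indicators, underweight and overweight–obese, each against normal weight. Convert each to points by the existing rule, oriented so that a higher WIC means better IC. Two indicators fit that rule, which turns one coefficient into one score; a spline would not. Add a sentence on how the two BMI terms are scored, including what happens if their coefficients differ in sign, since the rule rounds absolute values.

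The cost is wording, one extra model term and that scoring sentence. BMI is already to be measured and the article states that no data have been collected. The underweight coefficient will be imprecise if few participants are underweight: at the assumed 5%, 0.05 × 4,675 ≈ 234 people, with about 234 × 0.0495 ≈ 12 events if RR_u = 1 and 23 if RR_u = 2.

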#### Statistical models to assess whether IC is a predictor of ADLs/IADLs, falls, and death

Two Cox regression models will be evaluated to estimate the incidence rates of outcomes (i.e., functional loss measured by IADLs, falls, and death) associated with IC at baseline (e.g., TIC, DIC, and WIC) (ElHafeez et al., 2021). Cox’s first model has the indicator variable X to denote the association with each of the two groups of IC exposure at baseline (e.g., X1 = 1 for medium and high TIC and X1 = 0 for low TIC), with Y being the adverse incident at 3 years of follow-up (loss of ADLs/IADLs, falls, and death); survival times will be measured by the interval from the first assessment to the adverse incident. For subjects who do not experience an adverse incident, the follow-up time will be the last evaluation of the study.

The model also comprises a collection of covariates V with the potential to be a confounding factor in the association between Y and X (e.g., sociodemographic factors), and W would be the potentially interactive term between X and V (e.g., sex * TIC). The regression coefficient of X describes the effect of TIC on outcome Y, that is, the risk of greater or lesser loss of ADL/IADL, falls, and death for those exposed to medium or high TIC relative to those exposed to low TIC. The W terms will assess whether there is a positive interaction between TIC and one of the V confounders that have been identified to be potentially interacting. The model will extend by substituting TIC for DIC or WIC as the main exposure variable X. Alternatively, we can also model Y (e.g., IADL) as a function of X (either TIC, DIC, or WIC) and the same set of V and W using logistic regression to estimate the odds ratio of the outcomes.

We will evaluate the IC trajectory through changes in IC scores (∆IC or WIC) or the presence of IC decline (DIC) after 3 years, along with their associations with IADL outcomes, falls, and death. For example, the mean/median of ∆IC (or WIC) and the prevalence of DIC will be generated at baseline and at the end of the 3-year follow-up. We will then generate the mean/median or prevalence of IC measure by levels of ADL/IADL, falls, and death. The means/medians of IADLs and the incidence of falls and death after 3 years of follow-up will also be estimated.

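### The WIC points rule rounds coefficients before dividing, so a significant subdomain can score less than a non-significant one; WIC is also derived from IADL loss and then tested against it

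*Protocol article*

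**What the plan says.** Under *Generation of weighted IC score (WIC)*, each dichotomised subdomain is first screened against IADL loss. One whose chi-square p-value "is less than or equal to α = 0.25 will enter the multivariate logistic regression model", with adjustment for other factors; a few clinically essential items enter regardless. Subdomains whose adjusted p-values "are less than or equal to α = 0.05 (statistically significant) will be used to generate WIC as follows": points are formed by "dividing the coefficient by the smallest regression coefficient in the model after rounding the absolute value of the coefficient to the nearest integer value". For the rest, "Regression coefficients that are not statistically significant in the adjusted model will have a value of one (1) point". Points from all components are added, and terms are to be entered so that a higher WIC means better IC.

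The section on the IC composite index confirms that WIC is "derived from the multivariate regression result of the association between IC subdomains and IADL loss".

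In the section on IC as a predictor of ADLs/IADLs, falls and death, the Cox model comes first with TIC as exposure, and then "The model will extend by substituting TIC for DIC or WIC as the main exposure variable X". A logistic alternative is given: "we can also model Y (e.g., IADL) as a function of X (either TIC, DIC, or WIC"), with the same covariates. One cohort is described. The article mentions no split sample, external weights or correction for fitting and testing on the same outcome.

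**The concern.** Two separate things look wrong.

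**The arithmetic of the points.** Integer scores normally come from dividing each coefficient by a reference coefficient and then rounding. The printed sentence puts the rounding before the division. Log odds ratios for binary items are mostly small numbers, so rounding them to integers removes nearly all their information and turns many into 0. Since non-significant items are given 1 point, a subdomain shown to predict IADL loss can count for less than one that was not. The sentence also leaves open whether the divisor is rounded, whether *smallest* covers all coefficients or only significant ones, and whether it is meant in absolute or signed value. The last matters: with terms oriented so that higher is better, expected coefficients for IADL loss are negative, and the smallest signed value would belong to the strongest item.

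**The circularity.** The same outcome selects the items, sets their weights and then judges the score. The section on eligibility screens out significant ADL/IADL loss at entry, so baseline IADL status can hardly supply a separate fitting outcome. Both steps would draw on IADL loss during follow-up.

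At stake are whether WIC can be computed sensibly, and whether its association with IADL loss can be taken at face value.

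**Working it through.** The protocol gives no WIC figure or subdomain coefficient, so there is nothing to reproduce. The checks below use its rule and sample size, with assumptions marked.

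**1. Rounding thresholds.** |b| < 0.5 rounds to 0: exp(−0.5) = 0.61 and exp(0.5) = 1.65. |b| from 0.5 to 1.5 rounds to 1: exp(1.5) = 4.48, or the reciprocals for protective coding.

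**2. Can a significant item fall in the zero zone?** The smallest significant coefficient is approximately |b| = 1.96 / √(N·p(1−p)·q(1−q)).
- N = 5,500 × 0.85 = 4,675 (sample size section: about 5,500, dropout 15%).
- p = 4.95% (Table 1, unexposed incidence, used as the overall rate), or 1 − (1 − 0.0495)³ = 14.1% if that is a yearly rate (assumed).
- q = item prevalence, 10% to 50% (assumed).

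| p | q | smallest significant \|b\| | OR |
|---|---|---|---|
| 4.95% | 50% | 0.264 | 1.30 |
| 4.95% | 10% | 0.441 | 1.55 |
| 14.1% | 50% | 0.165 | 1.18 |
| 14.1% | 10% | 0.274 | 1.32 |

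Each value lies below 1.65, so a significant item can score 0.

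**3. The rule on an example.** Assumed significant ORs 1.3, 1.5, 1.9, 2.5, 3.0 have |b| = 0.262, 0.405, 0.642, 0.916, 1.099.

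| Reading | Points |
|---|---|
| Round numerator, divide by 0.262 | 0, 0, 3.81, 3.81, 3.81 |
| Round numerator and divisor | divisor 0, undefined |
| Divide by 0.262, then round | 1, 2, 2, 3, 4 |

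The first reading does not even give integers.

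**4. The divisor.** If the model also holds a non-significant coefficient of 0.05 (assumed) and that counts as the smallest, then even with divide-then-round OR 1.3 gets 0.262/0.05 = 5.2, or 5 points, and OR 1.9 gets 0.642/0.05 = 12.8, or 13, instead of 1 and 2.

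**5. How often items score 0.** Simulation with 14 correlated binary items, N = 4,675, prevalence 10–50%, 100 runs per setting, numerator only rounded:

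| Assumed true ORs | significant items scoring 0, p = 4.95% | p = 14.1% |
|---|---|---|
| 1.0–1.7 | 69% | 83% |
| 1.0–2.0 | 47% | 61% |
| 1.3–2.0 | 45% | 52% |
| 1.0–3.0 | 24% | 34% |
| 1.7–3.0 | 9% | 6% |

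If the divisor is rounded as well, the score is undefined in 93–100% of runs for the ranges starting at 1.0 or 1.3, and in 61–84% for 1.7–3.0.

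**6. Circularity with no true effects.** The score was derived and tested on the same IADL outcome using divide-then-round, because the printed order often cannot be computed. The false-positive rate at the 0.05 level depended heavily on coding:
- about 5–8% in the mildest variant, with the smallest significant coefficient as divisor;
- 10–16% in variants with the smallest coefficient in the model as divisor;
- about 21–38% when only screened items were summed and absolute values used;
- about 85–90% when screened items were also oriented by their fitted sign.

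On independent outcomes it was about 5–6.5%.

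**7. Circularity with true effects.** WIC log OR per SD, same data against new data:

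| Assumed item ORs | p = 4.95% | p = 14.1% |
|---|---|---|
| 1.0–2.0 | 0.76 vs 0.71 (+7%) | 0.75 vs 0.73 (+3%) |
| 1.0–1.7 | 0.58 vs 0.51 (+14%) | 0.57 vs 0.54 (+6%) |

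Every run remained significant in new data.

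**The case against.** The printed sentence is probably a slip for divide-then-round, since the 1-point rule for non-significant items makes sense only that way. That is likely, but a programmer following the text would get zeros or a failed computation, so the text still has to be corrected.

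A reader might infer that most significant subdomains would score 0. The documents do not support that. They give no subdomain coefficients, and the share ran from 6% to 83% over the assumed ranges. Table 1's risk ratios of 1.7, 1.91 and 3.0 describe low IC as a whole, not single items, and taken as odds ratios all three round to 1. Nor is an undefined score certain: it requires the divisor to be rounded too, and the sentence does not settle that.

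On circularity, optimism correction is often left to an analysis plan, which is not shown, and use of the same people is inferred from there being one cohort. Both are fair, but the article itself fixes IADL loss as both the deriving and the tested outcome. A complete absence of effects is also not the likely scenario, since the Rationale cites studies in which IC predicts ADL/IADL decline. No single false-positive rate should therefore be attached to the plan.

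A reader might also infer that the study's main hypotheses or its composite index are compromised. They are not. The research questions name TIC, DIC and ∆IC, not WIC, and the composite index is built without reference to any outcome.

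Finally, taking absolute values has a purpose, because correctly directed coefficients for IADL loss are negative under the stated orientation. What remains is that absolute values also credit an item pointing the wrong way.

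**Conclusion.** The concern stands, within limits. As printed, the rule can rank a significant subdomain (OR about 0.61 to 1.65) below a non-significant one, treats ORs from about 1.65 to 4.48 alike, and lets a near-zero coefficient set the scale. The thresholds are plain arithmetic. That significant items can fall in the zero zone rests on the planned sample size and the assumed event rates and prevalences. How many items would be affected, and whether the score would be undefined, cannot be determined from the document.

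The WIC–IADL association is optimistic because the same outcome builds and tests the score. Its size depends on the true effects and on the coding: modest in the scenarios with real effects, possibly large if effects are weak and items are oriented by their fitted sign. Falls and death were not used to fit WIC and are much less affected. The TIC and DIC hypotheses are unaffected.

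**What to change.** Restate the rule as: points = coefficient divided by the smallest statistically significant coefficient in absolute value, then rounded to the nearest integer. Set the sign so that an item in the expected direction earns positive points and a higher WIC means better IC, as the section already intends. With terms coded so that the better state is 1 and IADL loss as outcome, this means reversing the sign of the coefficient; dividing the signed coefficient as it stands would turn the score upside down. State that an item in the wrong direction earns no positive points.

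Report the WIC–IADL association only with cross-validation or bootstrap optimism correction in which the 0.25 screen, the 0.05 selection and the weighting are all repeated in each fold or resample. Otherwise, label it as apparent performance.

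The cost is one corrected sentence, some programming, and a slightly less favourable WIC–IADL estimate. The article states that no data have been collected, so the rule can still be fixed before any result is seen.
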